#### Hypothesis 1b: comparable clinical effectiveness of technical assistance methods

For student outcomes, multilevel models extend to three levels for repeated observation of marijuana use frequency and secondary outcomes (i.e., problems, motives, perceptions, self-efficacy to abstain, academic performance, and engagement) nested within interventionists. A primary test parameter is the interaction of time × technical assistance method of the TMCU interventionist as a dummy-coded predictor. As temporal effects may not conform to simple linear growth curves, models will test different specifications of time (i.e., piecewise, polynomial, or other nonlinear approaches). The a priori non-inferiority margin (i.e., ½ SD) will again be applied and, if exceeded, a test of superiority will specify the direction and magnitude of differential impact.

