### Units of analysis and measures

Trial measurement includes students nested in interventionist caseloads, which in turn are nested in schools. Units of analysis exist at three levels: school, interventionist, and student. Corresponding data collection instruments are listed in Table 2.

**Table 2 Tab2:** Trial measurement instruments and processes

Unit of analysis	Instrument/process	Respondent(s)	Timing of assessment
Schools			
	Implementation leadership scale [62]	School staff members	Trial outset
	Implementation climate scale [63]	School staff members	Trial outset
	Site visit including elicitation interview with school leadership	Principal, other leaders	Trial outset
	Exit interview	Principal, other Leaders	Trial conclusion
Interventionists			
	Demography and background	Interventionists	Pre-training
	MI knowledge/attitudes test [64]	Interventionists	Pre/post-training + 6-, 12-, 18-, 24-month
	Adoption readiness scale [65]	Interventionists	Pre/post-training + 6-, 12-, 18-, 24-month
	Fidelity-rated interaction with a standardized patient [66]	Interventionists	Pre/post-training + 6-, 12-, 18-, 24-month
	Training satisfaction survey	Interventionists	Post-training
	TA satisfaction survey	Interventionists	6-, 12-, 18-, 24-month
	Interventionist time-log	Interventionists	Weekly, over 24 months
Students			
	Demography and locator data	Students	Baseline
	Normative perceptions [67, 68]	Students	Baseline
	Life goals [69]	Students	Baseline
	Global Appraisal of Independent Needs [70]	Students	Baseline, 3- and 6-month
	Marijuana Problems Scale [71]	Students	Baseline, 3- and 6-month
	Marijuana Motives Measure [72]	Students	Baseline, 3- and 6-month
	Self-efficacy to Avoid Marijuana [73]	Students	Baseline, 3- and 6-month
	Student Academic Self-Report [74]	Students	Baseline, 3- and 6-month
	Student Engagement Instrument [75]	Students	Baseline, 3- and 6-month
Investigators			
	Technical Assistance Time-Log	Purveyor	Weekly, over 24 months
	Stages of Implementation Completion Checklist [76]	Research coordinator	Continual

Trial design proposes recruitment of approximately ten schools, with 2–4 interventionists recruited per participating school to garner an intended sample of TMCU interventionists (*N* = 30) randomized to ‘gold-standard’ or ‘as-needed’ technical assistance conditions; Self-referring students (*N* = 250) will be randomized in a 2:1 ratio to receive the TMCU intervention vs. waitlist/control

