#### Students

Trial measurement of 250 high school students to self-refer for randomization (in 2:1 ratio) to TMCU or waitlist/control includes baseline survey of demography, contact information, normative perceptions of marijuana use [60, 61], and life goals information [62] incorporated as personal feedback. Repeated-measures assessed in intervention outcome assessments (i.e., baseline, 3- and 6-month follow-up) include the following student-report instruments (1) Global Appraisal of Independent Needs [63], offering recent marijuana use and diagnostic symptoms; (2) Marijuana Problems Scale [64]; (3) Marijuana Motives Measure [65]; (4) self-efficacy to avoid marijuana use [66]; (5) Student Academic Self-Report, tapping homework completion, attendance, and disciplinary actions [67]; and (6) Student Engagement Instrument [68], measuring academic and social engagement. This will be supplemented by administrative data accessed from participating school districts. Students will receive financial remuneration to incentivize retention and completion of outcome assessments.

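### Perceptions is listed as a repeated secondary student outcome in Hypothesis 1b but is scheduled at baseline only, so its stated analysis cannot be run as written

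*Protocol article*

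**What the plan says.** All references are to the protocol article.

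**Analysis section.** Under Hypothesis 1b, "multilevel models extend to three levels for repeated observation of marijuana use frequency and secondary outcomes". The list that names those outcomes reads "secondary outcomes (i.e., problems, motives, perceptions, self-efficacy to abstain, academic performance, and engagement) nested within interventionists", with perceptions third. The test is then specified: "A primary test parameter is the interaction of time × technical assistance method of the TMCU interventionist as a dummy-coded predictor". The half-SD non-inferiority margin is applied to the results of these models.

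**Measurement schedule.** In Table 2 (Units of analysis and measures) the row reads "Normative perceptions [67, 68] Students Baseline". A row for an outcome that is repeated reads differently, for example "Marijuana Problems Scale [71] Students Baseline, 3- and 6-month". The Students subsection agrees with the table. Its account of student measurement "includes baseline survey of demography, contact information, normative perceptions of marijuana use [60, 61], and life goals information [62] incorporated as personal feedback", and it then gives a separate numbered list of six instruments repeated at baseline, 3 and 6 months. Normative perceptions is not among the six. The Baseline student assessment subsection also mentions perceptions, as part of the data gathered for the personal feedback report.

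**The concern.** A growth model needs at least two measurements per student. The analysis section commits to such a model for perceptions, while the schedule supplies one measurement, taken before TMCU delivery. The model would have no change to estimate, and the non-inferiority margin would have nothing to be compared with.

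At stake is one declared secondary outcome. If the conflict is left, that outcome will go unreported, and a later reader comparing the article with the results could take this for selective reporting. An analysis plan cannot repair it, because it cannot supply data that were not collected.

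**Working it through.** The point rests on no sample size, alpha or power figure, so there is no figure in the plan to reproduce. The check has two steps.

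**Step 1. Match each outcome named under Hypothesis 1b to its instrument and timing in Table 2 and the Students subsection.**

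| Outcome under Hypothesis 1b | Instrument | Time points |
|---|---|---|
| Marijuana use frequency | Global Appraisal of Independent Needs | 3 |
| Problems | Marijuana Problems Scale | 3 |
| Motives | Marijuana Motives Measure | 3 |
| Perceptions | Normative perceptions | 1 |
| Self-efficacy | Self-efficacy to Avoid Marijuana | 3 |
| Academic performance | Student Academic Self-Report | 3 |
| Engagement | Student Engagement Instrument | 3 |

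Three time points means baseline, 3 and 6 months; one means baseline. Perceptions therefore has 0 of 2 planned follow-ups, and it is 1 of 6 secondary outcomes.

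The table and the text describe the same perceptions measure. Their reference numbers differ (67 and 68 in the table, 60 and 61 in the text), but the same shift of 7 separates the other student instruments, for example 71 and 64 for the Marijuana Problems Scale.

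**Step 2. Ask whether the test parameter is estimable.** Write the fixed part of the model as

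E(Y) = b0 + b1·t + b2·A + b3·t·A,

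with t the time in months and A = 0 or 1 for the technical assistance method. The parameter of interest is b3.

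- Baseline only: t = 0 for every record, so the columns for t and t·A are all zero. The design matrix has rank 2 of 4. Only b0 and b2 can be estimated, and b2 is then a baseline difference between the two methods' caseloads, which is not an effect of technical assistance over time.
- Times 0, 3 and 6: the design matrix has rank 4 of 4, and b3 can be estimated.

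A numerical rank calculation gave the same values, 2 and 4. The result does not depend on the linear form: a piecewise or polynomial time term, which the section also allows, has no variation when there is a single time point.

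The same gap rules out a comparison of TMCU with waitlist/control on perceptions at 3 or 6 months, since neither visit carries the measure.

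**The case against.** The mismatch itself is hard to dispute. The fair case on the other side concerns its weight.

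- **It may be a carried-over word.** The Baseline student assessment subsection lists problems, motives, perceptions and self-efficacy in the same order as Hypothesis 1b. Two concordant schedule statements against one list suggest that the word slipped in. This is plausible, but it is an inference: the article does not say which section is wrong, and on either reading the text needs correcting.
- **Nothing central depends on it.** The student hypothesis names marijuana use frequency, the cost-effectiveness unit is days of use, and Table 1 does not list perceptions among the TMCU outcomes. This stands, and it limits the size of the point.
- **The list of repeated instruments might be open, or another instrument might hold perception items.** The list is numbered, Table 2 schedules normative perceptions separately at baseline only, and no other student perceptions measure is named. This does not stand.
- **It may be a broken table or a detail left to another document.** The prose and the table agree, and both the schedule and the outcome list are stated in the article. This does not stand.

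A reader might also infer three stronger things. The first is that perceptions is a mechanism of the intervention, so that losing it damages the trial's explanatory aim. The article states no mediation aim for perceptions and gives the measure the role of feedback input. The second is that the whole outcome is lost once follow-up starts. Students enrol over 24 months and are assessed by web survey, so a late addition would lose only the visits already completed. The third is that adding the items is the better remedy. Nothing in the article shows which option the investigators intended.

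**Conclusion.** The point holds as an internal contradiction between the outcome list and the assessment schedule. As written, the time by technical-assistance interaction cannot be estimated for perceptions, and neither can a TMCU versus waitlist/control comparison at follow-up.

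Its size is one of six secondary student outcomes. Marijuana use frequency and the other five secondary outcomes each have three scheduled assessments, and the power statement does not rest on perceptions. No primary conclusion changes.

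Two assumptions are made. One is that perceptions under Hypothesis 1b means the normative perceptions measure, the only student perceptions measure listed. The other is that the trial status is as the article reports it: school recruitment under way and interventionist enrolment still to come, so student follow-up has not begun.

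**What to change.** Reconcile the sections before the first 3-month student assessment, by either of two changes:

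1. Add the normative-perception items to the 3- and 6-month web surveys, and amend the Table 2 row and the list of repeated instruments in the Students subsection. The cost is a few extra items per student at each follow-up.
2. Delete perceptions from the outcome list under Hypothesis 1b, and state that it serves only as baseline feedback data or as a baseline covariate. The cost is one word removed and one sentence added.

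The choice belongs to the investigators and depends on whether they mean to report change in perceptions. If the first option is taken after follow-up has started, record the date of the change and report how many completed visits lack the measure.

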### Hypothesis testing and analytic approach

Hypotheses focus on comparative utility of two technical assistance methods on implementation outcomes among TMCU interventionists and intervention effectiveness among students. Hypothesized effects are that the (1) longitudinal effects of interventionists receiving ‘gold-standard’ vs. ‘as-needed’ technical assistance will not differ, with the latter method proving more cost-beneficial and cost-effective; and (2) effects of technical assistance method for intervention impact on student marijuana use frequency will not differ, with greater reduction expected of students randomly assigned to TMCU vs. waitlist/control.

Trial analyses will be governed by an investigative team member (KK), experienced as a biostatistician and methodologist in adolescent health research. Given nesting of trial data (i.e., repeated observations of students, nested in interventionist caseloads; interventionists nested in schools), multilevel models will include progressive taxonomies in model-building. Initially, an unconditional model will estimate variance of random effects, and a subsequent unconditional growth model will identify the appropriate shape of and variability in rate of change over time for hypotheses involving repeated measures. Technical assistance condition will then be included in conditional models with predictors, with relevant covariates added to determine robustness of main effects and relative goodness-of-fit for each successive model via likelihood ratio tests and deviance statistics. Power analyses (.80, *p* < .05) inform proposed recruitment of (1) 30 interventionists to detect longitudinal effects of training and technical assistance consistent with those for other lay counselors (Cohen’s *d* = 1.00); and (2) 250 students to detect small intervention effects (Cohen’s *d* = .35) relative to waitlist/control.

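### Hypothesis 1b applies a ½ SD margin to a time × assistance-method parameter whose form of time is chosen from the data, without fixing which coefficient or time point is tested

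*Protocol article*

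**What the plan says.** All references are to the Protocol article.

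- **Test parameter** (Hypothesis 1b): "A primary test parameter is the interaction of time × technical assistance method of the TMCU interventionist as a dummy-coded predictor". No visit or contrast is attached to it.
- **Form of time** (same section): the reason given is "As temporal effects may not conform to simple linear growth curves", and so "models will test different specifications of time (i.e., piecewise, polynomial, or other nonlinear approaches".
- **Margin** (same section): "The a priori non-inferiority margin (i.e., ½ SD) will again be applied and, if exceeded, a test of superiority" follows.
- **Visits** (Students, under Units of analysis and measures): "i.e., baseline, 3- and 6-month follow-up", which is three occasions.
- **How the shape is found** (Hypothesis testing and analytic approach): "a subsequent unconditional growth model will identify the appropriate shape of and variability in rate of change over time". Assistance condition is added after that step, and successive models are compared by likelihood ratio tests and deviance.

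**The concern.** A non-inferiority test needs one quantity, in the units of its margin, fixed before the data are seen. Here the margin is half an SD of an outcome, while the parameter is an interaction with time whose form is still to be found.

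Once the form is not a straight line, time × method is no longer a single number with a fixed meaning. It may be a slope at baseline, a pair of slopes, or a pair of visit differences. The comparison of methods on intervention effectiveness is one of the trial's co-primary aims. If the methods differ in a way that is not linear in time, the same data could pass or fail non-inferiority according to which coefficient is read.

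**Working it through.** The document gives no figure for this parameter, so there is none to reproduce. The check is algebra, followed by an illustrative simulation.

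**Inputs from the document.** Visits at 0, 3 and 6 months; margin 0.5 SD; two-sided 95% confidence interval (stated under Hypothesis 1a); 250 students allocated 2:1.

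**Assumptions.** The method comparison uses TMCU students split evenly: 250 × 2/3 ÷ 2 ≈ 83 per method. Outcome SD is 1 at each visit, with the same correlation r between any two visits (0.5, range 0.3 to 0.7). There is no clustering or dropout.

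**Step 1: what three visits can support.** Let d0, d3, d6 be the between-method differences at each visit, positive meaning more use under as-needed assistance. A straight line has one interaction coefficient. Quadratic, two-piece and categorical time each have two, which reproduce d3 − d0 and d6 − d0 exactly. These three are one saturated mean model. Under the same random-effects structure they have equal likelihood, so deviance cannot choose among them.

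**Step 2: what each coefficient measures.**

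- Linear slope: (d6 − d0)/6
- First piece: (d3 − d0)/3; second piece: (d6 − d3)/3
- Linear term of a quadratic coded from baseline: (−3·d0 + 4·d3 − d6)/6

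Scaled to SD units (linear and quadratic × 6 months, each piece × 3 months):

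| (d0, d3, d6) | Linear | Piece 1 | Piece 2 | Quadratic, slope at baseline |
|---|---|---|---|---|
| (0, 0.25, 0.5) | 0.50 | 0.25 | 0.25 | 0.50 |
| (0, 0, 0.5) | 0.50 | 0 | 0.50 | −0.50 |
| (0, 0.5, 0) | 0 | 0.50 | −0.50 | 2.00 |

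In the first row every version has the same slope, 0.5/6 = 0.083 SD per month. Even so, that slope is 0.25 SD over 3 months and 0.5 SD over 6. The margin cannot be attached to it until the horizon is stated.

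**Step 3: precision at r = 0.5.** The variance of a contrast c is (1 − r) × Σc² × 2/83.

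- 0–6 month change or either piece, c with Σc² = 2: √(0.5 × 2 × 2/83) = 0.155
- Baseline slope × 6, c = (−3, 4, −1), Σc² = 26: √(0.5 × 26 × 2/83) = 0.56

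**Step 4: chance of declaring non-inferiority** (upper 95% limit below 0.5 SD; 20,000 simulated trials, r = 0.5):

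| True (d0, d3, d6) | Linear × 6 | Piece 1 × 3 | Piece 2 × 3 |
|---|---|---|---|
| (0, 0, 0.5) | 2.3% | 90% | 2.5% |
| (0, 0.5, 0) | 89% | 2.6% | 100% |

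Hand check of the 90%: Φ(0.5/0.155 − 1.96) = Φ(1.26) ≈ 0.90. For r from 0.3 to 0.7 that entry runs from 78% to 99%, while the linear entry beside it stays near 2.5%.

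**The case against.** The strongest reply has four parts.

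- **The shape is not chosen for its between-method result.** It comes from a growth model without assistance condition. This stands. A reader might infer that the plan lets analysts search for a shape that yields non-inferiority; the document does not support that. The step still leaves open which coefficient is tested when the shape is curved.
- **The saturated forms agree on the fitted differences.** Quadratic, two-piece and categorical time give identical differences at 3 and 6 months. With complete balanced data and equal correlations, the linear model's 0–6 month change is also d6 − d0. This stands too, and it places the fault in the unnamed contrast rather than in the fitted curves.
- **The extreme figures rest on readings that no section states.** Nothing says the margin would be applied to the baseline slope of a quadratic or to the first piece alone. Hypothesis 1a speaks of between-method differences and lists pre–post change, mean level and rate of change. That makes the worst case less likely, but the list is given for interventionists, has three members, and does not settle Hypothesis 1b. It would also be too strong to say that the sign of the parameter depends on the shape in general: when the difference is linear in time, all the versions in the first table share a sign. The text says a primary parameter, not the only one.
- **A SAP may settle it.** Coding and contrasts are often left there. But the article does not leave the form of time unmentioned; it commits to testing alternatives and applies a margin to the result. A SAP that followed it literally would inherit the problem.

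A reader might also argue that three visits cannot identify the model, because three random growth terms with unstructured covariance plus a residual need 6 + 1 = 7 variance parameters against 6 distinct entries in a 3 × 3 covariance matrix. That holds only for that fully random structure, which the document does not specify.

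**Conclusion.** The point holds in a limited form. Hypothesis 1b ties a ½ SD margin to an interaction whose form of time the data will choose, and it fixes no contrast or time point. Choosing the shape before assistance condition is entered reduces selection on the result but does not define the parameter. If the shape is not linear, fit statistics cannot separate the saturated parameterisations, whose coefficients answer different questions.

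The size depends on how the methods differ over time. For a difference confined to 6 months and equal to the margin, the illustration gives 2.3% against 90% for two readings of the same data. These percentages rest on the assumed even split, equal correlations and absence of clustering and dropout; the algebra in Steps 1 and 2 does not. They show what the wording permits, not what the sponsor intends. This should be corrected, and it does not invalidate the design.

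**What to change.** In Hypothesis 1b, treat visit as categorical (0, 3, 6 months) and name one test quantity in advance: the between-method difference in days of marijuana use at 6 months, adjusted for baseline use, with clustering by interventionist kept in the model. Apply the ½ SD margin to that quantity only. Report growth-curve shapes as exploratory description.

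**Cost.** One extra time parameter. Under the assumptions above, precision is not lost: the standard error is √((1 − r²) × 2/83), which is 0.148, 0.134 and 0.111 at r = 0.3, 0.5 and 0.7. The linear 0–6 month change has 0.184, 0.155 and 0.120.

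The target does move from a growth rate to a 6-month difference. Students enrol after interventionists have been randomized to an assistance method, so baseline use could differ between methods, and a baseline-adjusted difference and a change score need not agree. Report the change-from-baseline contrast as a sensitivity analysis. By the article's account of current status, interventionist enrolment had not begun, so at that point the change was one of wording only.

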### A key challenge for implementing TMCU in schools

As in other health fields, experimental controls inherent in adolescent treatment trials limit generalizability of resulting findings [32]. This is prominent among reasons for ‘voltage drop,’ where effect size diminishes upon a therapy’s community implementation [33]. Though public demand for school-based services like TMCU is strong, the prospect of real-world TMCU implementation raises concerns about identification, training, and oversight of school-based personnel. Extant research on MI training conducted with a diverse workforce documents: (1) insufficiency of workshop training to cull durable skills [34, 35], and (2) utility of post-workshop technical assistance via coaching and performance-based feedback [36–38]. While such technical assistance is broadly recommended to disseminate health services [39–41], key questions for schools at which TMCU is implemented are how much technical assistance personnel require.

Given prominent concern about costs [42, 43], much may be gained from identifying affordable strategies to avail technical assistance [44]. In efficacy trials, gold-standard technical assistance includes fidelity monitoring, provision of feedback on work-samples, and recurrent behavioral rehearsal opportunities [45]—all to assure research therapists maintain sufficient fidelity [46]. Such gold-standard technical assistance was included for research therapists in TMCU efficacy trials [27–30]. Given scant resources at many schools, the prospect of replicating such procedures in support of TMCU implementation is understandably daunting. A consequent challenge is to identify alternative strategies whereby technical assistance is offered to resource-challenged schools without compromise to TMCU fidelity [47].

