**Fig. 1 Fig1:**
[figure not shown]
Fidelity drift alarm

The trial design described herein reflects a protocol funded by the National Institute on Drug Abuse (R01 DA040650, A Hybrid Effectiveness-Implementation Trial of a School-Based Teen Marijuana Check-Up). A hybrid type II trial [53], co-primary aims are to compare technical assistance methods for school-based TMCU interventionists on implementation outcomes and intervention effectiveness. School leaders will identify staff to be trained and serve as interventionists, then randomized to receive technical assistance over a 2-year period via (1) a ‘gold-standard’ group session occurring weekly, or (2) ‘as-needed’ individual sessions, triggered by a fidelity drift alarm calibrated by process control benchmarking. Self-referring students will be randomized, in 2:1 ratio, to TMCU or waitlist/control. Hypothesized effects are for non-differential impact of technical assistance methods on interventionists’ TMCU fidelity and marijuana use among TMCU-exposed students. Other expectations are for lesser cost of ‘as-needed’ technical assistance, and clinical effectiveness of TMCU relative to waitlist/control.

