#### Hypothesis 1a: comparable utility of technical assistance methods

A non-inferiority paradigm, traditionally used to show a novel treatment is not statistically different than an established one, will test study hypotheses. This paradigm will be applied to interventionists’ longitudinal implementation outcomes, principally TMCU fidelity (i.e., R:Q, %OQ, %CR) in SP interactions but also secondary outcomes of TMCU knowledge, attitudes, adoption readiness, and satisfaction. Initial effects are consistent with training intent, with analyses testing if ‘gold-standard’ and ‘as-needed’ technical assistance produce equivalent longitudinal impacts. If (as expected) the number of schools recruited is small, they will be dummy-coded and treated as fixed effects. Point-estimates and confidence intervals from the model will be included in non-inferiority tests, examining each technical assistance method for (1) pre-post change in implementation outcomes, (2) mean implementation level by TMCU interventionists over time, and (3) differential rate of change in implementation over time. As recommended [75], a ½ standard deviation (SD) difference will serve as the a priori non-inferiority margin. If the lower bound of two-sided 95% confidence interval of between-method differences exceeds this margin, a test of superiority will specify the direction and magnitude of differential impact of the technical assistance methods.

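### The student claim of comparable clinical effectiveness rests on the ½ SD non-inferiority test alone and is not made conditional on TMCU beating waitlist, so it would usually be met even if TMCU had no effect in schools.

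*Protocol article*

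**What the plan says.** The Background paragraph after Figure 1 makes comparison of the two assistance methods, on implementation outcomes and on intervention effectiveness, the co-primary aims. It then adds: "Other expectations are for lesser cost of ‘as-needed’ technical assistance, and clinical effectiveness of TMCU relative to waitlist/control".

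The section Hypothesis testing and analytic approach puts both student results in its second hypothesis: "effects of technical assistance method for intervention impact on student marijuana use frequency will not differ, with greater reduction expected of students randomly assigned to" (the contrast named there is TMCU against waitlist). It sizes the student sample on the waitlist contrast: "250 students to detect small intervention effects (Cohen’s *d* = .35) relative to waitlist/control".

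Hypothesis 1a sets the margin, "a ½ standard deviation (SD) difference will serve as the a priori non-inferiority margin", and the interval, a two-sided 95% confidence interval for the between-method difference. Hypothesis 1b carries the margin over to students, with the time by method interaction as a primary test parameter: "The a priori non-inferiority margin (i.e., ½ SD) will again be applied and, if exceeded, a test of superiority will specify the direction and magnitude". The superiority test named there is between the two methods, not between TMCU and waitlist.

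No section says that the conclusion about the methods depends on the waitlist comparison.

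**The concern.** The method comparison is made among students who received TMCU. A non-inferiority result there supports a statement about preserved effectiveness only if there was an effect to preserve. If school-delivered TMCU achieves nothing under either method, the two groups do not differ in truth, and a test designed to show a small difference will tend to succeed. The trial could then report that the as-needed method is clinically as effective as the gold-standard method beside a null comparison with waitlist. The first result would support moving schools to the cheaper method.

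The article itself gives a reason to guard against a weak effect. It names "voltage drop,’ where effect size diminishes upon a therapy’s community implementation" as a known problem. The trial also has what is needed for the guard: students are randomized 2:1 to TMCU or waitlist, and waitlisted students receive TMCU only after six months, so the control is concurrent through the last follow-up. The stated rule does not use it.

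**Working it through.** **Inputs from the article.** 250 students at 2:1, so about 167 TMCU and 83 waitlist; 30 interventionists; margin 0.5 SD; two-sided 95% interval; design effect d = 0.35 against waitlist; retention of 90% or more in earlier trials, giving 150 and 75.

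**Assumptions.** The article gives no interventionist ICC, so 0, 0.05 and 0.10 are shown. Students and interventionists are taken as split evenly between methods. The outcome SD is 1, and the contrast is a simple mean difference standing in for the time by method interaction.

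**The plan's own figure.** The stated basis is "Power analyses (.80, *p* < .05) inform proposed recruitment of" 250 students for d = 0.35. Sidedness is not stated. Two-sided 0.05 with equal allocation gives power 0.79 at 250 (258 needed), close to the stated 0.80. At the planned 2:1 ratio, two-sided, SE = √(1/83 + 1/167) = 0.134 and power is 0.74 (about 291 needed). At 75 and 150, SE = 0.141 and power is 0.69. These are before any clustering.

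**Step 1: chance of meeting non-inferiority when TMCU has no effect.** The true between-method difference is 0.

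- Design effect: DE = 1 + (n/30 − 1) × ICC.
- Standard error: SE = √(4/n × DE).
- Probability: P(T > 2.048), where T is noncentral t with 28 df and noncentrality 0.5/SE.

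| TMCU students | ICC | DE | SE | 0.5/SE | Probability |
|---|---|---|---|---|---|
| 167 | 0 | 1.00 | 0.155 | 3.23 | 0.88 |
| 167 | 0.05 | 1.23 | 0.171 | 2.92 | 0.80 |
| 167 | 0.10 | 1.46 | 0.187 | 2.68 | 0.73 |
| 150 | 0 | 1.00 | 0.163 | 3.06 | 0.84 |
| 150 | 0.05 | 1.20 | 0.179 | 2.80 | 0.77 |
| 150 | 0.10 | 1.40 | 0.193 | 2.59 | 0.70 |

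A simulation with 30 caseloads gives 0.69 to 0.88 over the same range.

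**Sensitivity.** Suppose the contrast is change from baseline and the margin is in baseline SD units. A normal approximation over ICC 0 to 0.10 at 90% retention then gives 0.59 (baseline correlation 0.3) to 0.98 (correlation 0.7). It falls to about one half only at ICC 0.20 with correlation 0.3.

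**Step 2: the same case with the claim conditional on superiority to waitlist.** With no TMCU effect, a two-sided 0.05 test favours TMCU with probability 0.025. The joint claim cannot exceed that; the simulation gives 0.020 to 0.025.

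**Step 3: cost when TMCU works as planned (d = 0.35) and the methods are equal.** Superiority power times the Step 1 probability:

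- Full retention, ICC 0: 0.74 × 0.88 ≈ 0.65.
- 90% retention, ICC 0.05: 0.69 × 0.77 ≈ 0.53.
- 90% retention, ICC 0.10: 0.69 × 0.70 ≈ 0.49.

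These products, taken before rounding, ignore clustering in the waitlist comparison. A simulation that includes it gives 0.50 and 0.45 for the last two.

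**The case against.** The strongest objection is that this is an omission from a condensed article. Testing order often sits in an analysis plan, and the plan, which is not shown, may contain such a condition. It is right that nothing in the article says the claim will be made whatever the waitlist result, and a reader should not infer that. What remains is that the article does set out the student rule (margin, test parameter and follow-up test) without the waitlist arm, and ranks the waitlist comparison among other expectations. Applied as written, the rule supports the claim without it.

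Second, the two results share one hypothesis, the sample is sized on the waitlist contrast, and the cost-effectiveness ratio is TMCU against waitlist, so a null result would be visible. That is fair, but the hypothesis joins the two only as an expectation, and reporting results side by side does not make one depend on the other.

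Third, a required gate is costly, and failing a test with power near 0.7 does not show absence of effect. This stands. It is why the fallback wording should be that comparative effectiveness is not established, not that TMCU failed.

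Fourth, the gate pools both methods. As-needed delivery could lose much of its effect, pass the pooled gate and still lie inside a 0.5 SD margin. This also stands, and it limits what the fix achieves.

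**Conclusion.** The concern holds in a bounded form. The stated rule lets comparable clinical effectiveness be concluded from the ½ SD test alone. With no TMCU effect it would be met about 0.70 to 0.88 of the time, given the assumed ICC of 0 to 0.10, the even split and the mean-difference approximation.

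Two stronger readings are tempting, and the documents do not support them. One is that the test is met automatically when TMCU does nothing. It is not: the figures are well short of 1, and can be lower if the baseline correlation is weak or the ICC large. The other is that the protocol predicts no effect in schools. Its remark on loss of effect is general and speaks of a diminished effect, not a zero one. The null case is a stress test of the rule, not a forecast.

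The size of the margin is a related but separate matter. At 0.5 SD it exceeds the 0.35 SD effect the trial is sized to detect, so it cannot supply the missing safeguard.

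**What to change.** State in Hypothesis 1b, or in the analysis plan, that comparable clinical effectiveness among students is claimed only if both hold:

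1. TMCU is superior to the concurrent waitlist on marijuana use frequency, two-sided 0.05.
2. The as-needed method meets the non-inferiority criterion against the gold-standard method, using the two-sided 95% interval.

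Both are required, so no alpha split is needed. If the first fails, report the between-method difference and each method's difference from waitlist with 95% confidence intervals, and describe the methods' comparative effectiveness as not established. Giving each method's difference from waitlist when the first succeeds would also help, because the pooled result does not show that each method kept the effect. The ½ SD margin for students still needs its own justification.

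The change is wording only, with no new data or participants. The article reports that interventionist enrollment had not begun, so on that status it could be made before outcome data existed. The price is the lower chance of making the claim shown in Step 3 of the working, and it should be stated openly.
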